### Feasibility

Number and percent will be used to summarize enrollment, randomization, assessment completion, intervention completion, and MBI session attendance. Additionally, the sociodemographic and clinical characteristics of those observable subjects in the MBI condition who complete four or more intervention sessions will be compared with those who complete less than four.

### Acceptability

Acceptability will be determined by qualitative analysis of semistructured interviews using an inductive data-driven approach. This will allow for extraction of core themes, as recommended by, for example, Hsieh and Shannon [48], for cases when theory or research literature is limited. Qualitative content analysis is selected because it is a widely and successfully used method for qualitative data analysis [49]. A multistage analytic strategy has been developed for qualitative analysis. In step 1, digital recordings will be transcribed verbatim. In step 2, transcripts will be imported into Atlas.ti software and then read and reread by three study personnel familiar with the content of the MBI, and text passages that appear to be relevant with regard to the research questions will be extracted and coded (i.e., labeled as a term preferably close to the text passage itself). Further relevant text passages will be subthemed under an existing term or assigned a new term if they do not fit into an existing category. In this style, the first two transcripts will be coded. In step 3, the emerging categories will be reviewed and critiqued by the three study personnel in a group discussion and revised. In step 4, the first two transcripts will be recoded on the basis of the discussion, and the next two transcripts will be coded on the basis of adjustments to the coding scheme determined by the three coders. In step 5, the three study personnel will reassemble to discuss the first four interviews and any new emergent codes. In step 6, the remaining five interviews will be coded.

### Efficacy

Descriptive statistics will be used to summarize the five measures at baseline and weeks 1, 3, and 6 for randomized participants with at least one outcome assessment completed (observable cases). Tables for unadjusted mean scores for each condition by time will be presented. Random coefficients regression models, a type of hierarchical mixed-effects model for longitudinal data, will be used to evaluate the trajectory of change in pain catastrophizing total scores and other pain-related outcomes. Nonlinear temporal patterns will be fitted as needed. The models will be used to examine the pattern of change in each outcome over time and estimate effect sizes.

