## Methods/design

### Overview

We are conducting a single-site pilot RCT comparing MBI and a wait-listed control condition with assessments at four time points (baseline, week 1, week 3, and week 6) in adult patients with SCD and chronic pain. Individuals who provide written informed consent will be enrolled and randomized to an MBI or control condition. The MBI will be conducted as a ten-person group teleconference call led by a certified MBI instructor. A 2:1 treatment allocation will be implemented in this initial pilot study to collect more data on the feasibility and acceptability of the MBI. Feasibility will include measures of enrollment, randomization, attendance, and intervention completion along with assessment completion. Acceptability will be assessed with semistructured interviews conducted with randomly selected MBI participants. The primary efficacy outcome will be pain catastrophizing total score.

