#### Setting and sample

Patients will be recruited from an outpatient comprehensive SCD center in the southeastern United States. An interdisciplinary team of physicians, nurses, psychologists, and social workers run the center, providing care for approximately 600 adults with SCD. The target sample for this pilot study is 60 patients with SCD and chronic pain, with 40 patients randomly assigned to receive the MBI and 20 patients to the control condition. With a sample size of 60, the study does not have 80% power to detect a significant difference between the MBI and control conditions on the primary outcome of pain catastrophizing with a level of significance set a 0.05 (two-tailed). However, the focus of this pilot study is to estimate treatment effect sizes rather than to conduct statistical significance testing.

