### Randomization procedures

Patients who provide informed written consent and meet the participant selection criteria will be enrolled and randomized using a 2:1 treatment allocation to either the MBI or control condition. Because the MBI condition is group-based, randomization of participants will be divided into 4 cohorts of 15 participants to reduce the amount of idle time between informed consent and intervention delivery. After the first cohort of 15 participants provides informed consent, they will be randomly assigned either to receive the MBI (*n* = 10) or to a control condition (*n* = 5). The random number function in Excel 2007 software (Microsoft, Redmond, WA, USA) will be used to randomize patients to either the MBI (*n* = 40) or control (*n* = 20) condition using a permuted block randomization scheme to achieve a 2:1 allocation. Within each block size of 15, 10 patients will be randomized to receive the MBI and 5 will be randomly assigned to the wait-listed control condition.

Within 2 weeks of randomization, participants will begin the MBI or their time in the control condition. Following randomization and initiation of the first cohort of 15 patients, the next cohort of 15 patients will be recruited and randomized following the same protocol. This will continue until 60 participants are randomized in a total of 4 cohorts.

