Table 1 summarizes the intervention that will be used in this study and compares it with typical MBSR programs. The first 10 minutes of each session will be used to review previous material, followed by approximately 20 minutes of instruction and overview of a new mindfulness exercise and 15 minutes of mindfulness practice, with the remaining time used for questions. Because each session will be conducted as a group teleconference call, the size of each MBI session is limited to a maximum of ten patients (plus the mindfulness instructor) to minimize caller interruptions and disruptions.

**Table 1 Tab1:** Comparison between typical mindfulness-based stress reduction program and telephonic mindfulness-based intervention for persons with sickle cell disease

Week	MBSR	Telephonic MBI
1	Body scan	Mindful breathing
2	Breath awareness	Body scan
3	Sitting meditation, individual yoga	Loving-kindness
4	Stress coping	Mindful eating
5	Communication styles	Sensory awareness
6	Yoga, sitting meditation	Overview, conclusion
7	Loving-kindness	N/A
Weekend Retreat	Silent retreat	N/A
8	Wrap-up	N/A

*MBSR* Mindfulness-based stress reduction, *MBI* Mindfulness-based intervention, *N/A* Not applicable

This table provides a comparison of the standard 8-week MBSR program and the telephonic MBI that will be tested

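### The stated efficacy model makes no allowance for MBI call groups or for the cohort blocks; precision is modestly overstated if outcomes within a call group are positively correlated

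*Protocol article*

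**What the plan says.** - **Delivery.** The Overview states: "The MBI will be conducted as a ten-person group teleconference call led by a certified MBI instructor". The description of the MBI condition adds that "the size of each MBI session is limited to a maximum of ten patients". One instructor leads every session.
- **Control.** Wait-listed patients receive treatment as usual and attend no group sessions during the comparison period (Wait-listed control condition).
- **Randomization.** The Randomization procedures section gives the structure and its reason: "Because the MBI condition is group-based, randomization of participants will be divided into 4 cohorts of 15 participants". It fixes the split as well: "Within each block size of 15, 10 patients will be randomized to receive the MBI and 5 will be randomly assigned", these five being the controls. The total is 60, "with 40 patients randomly assigned to receive the MBI and 20 patients to the control condition" (Setting and sample).
- **Analysis.** The Efficacy section that follows Analytic approaches says: "Random coefficients regression models, a type of hierarchical mixed-effects model for longitudinal data, will be used to evaluate the trajectory of change". This covers the primary outcome and the other pain-related outcomes. It describes the model as one for longitudinal data, used to examine patterns over time and to estimate effect sizes. It names no call-group or cohort term.
- **Purpose.** Setting and sample and Analytic approaches both put effect-size estimation ahead of significance testing. Analytic approaches still provides for two-sided tests at 0.05 where testing is done.

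**The concern.** This is a partially nested design. The 40 MBI patients are treated in four groups and share sessions and peers; the 20 controls are not grouped at all. A model whose only hierarchy is time within patient treats the 40 as independent. If patients on the same call come to resemble one another after the sessions begin, the MBI mean is less precise than that model reports.

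The article itself treats the grouping as important elsewhere: it shapes the randomization, and the interview sample is drawn from each of the four cohorts. It does not reach the description of the efficacy model.

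At stake is the precision attached to the effect sizes. A pilot meant to inform later MBIs passes on both an estimate and its uncertainty, and a later group-delivered trial would have to allow for clustering in its sample size. Any p-values that are reported would also be affected. Cohort raises a different question: it is the randomization block, and a model without it does not use the blocking that the design provides.

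**Working it through.** **Inputs from the article:** four cohorts of 15, each split 10 MBI to 5 control; 40 MBI and 20 control in total; at most ten per call group; two-sided 0.05.

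**Assumed:** ICC values of 0.02, 0.05 and 0.10 (the article gives none); full groups of ten; one time point with common unit variance.

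**The plan's own figures.** The allocation reproduces: 4 × 15 = 60, 4 × 10 = 40, 4 × 5 = 20. The statement that power is below 80% cannot be reproduced, because no effect size or standard deviation is given. For reference, 40:20 without clustering has 80% power at a standardized difference of (1.960 + 0.842) × √(1/40 + 1/20) = 0.767.

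**Step 1: MBI call group ignored.**

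- Naive variance of the difference: 1/40 + 1/20 = 0.0750.
- Variance allowing for groups: (1 + 9 × ICC)/40 + 1/20.
- True type I error, normal approximation: 2 × [1 − Φ(1.96 / SE ratio)].

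| Assumed ICC | Design effect | Effective MBI n | Variance | True SE / naive SE | Type I error |
|---|---|---|---|---|---|
| 0.02 | 1.18 | 40/1.18 = 34 | 0.0795 | √1.06 = 1.030 | 5.7% |
| 0.05 | 1.45 | 40/1.45 = 28 | 0.08625 | √1.15 = 1.072 | 6.8% |
| 0.10 | 1.90 | 40/1.90 = 21 | 0.0975 | √1.30 = 1.140 | 8.6% |

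The true SE is 3%, 7% and 14% larger than the naive one. Put the other way, the naive SE is 3%, 7% and 12% too small (1 − 1/1.140 = 0.12). The difference detectable with 80% power moves from 0.767 to 0.790, 0.823 and 0.875.

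**Step 2: smaller analysed groups.** With seven per group and 28:14 analysed, the SE ratios are √1.04 = 1.02, √1.10 = 1.05 and √1.20 = 1.10, and type I error is 5.5%, 6.2% and 7.4%.

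**Step 3: cohort ignored, no call-group effect.** A cohort effect shared by both arms cancels from the difference because every block is 10:5. With cohort ICC c, the true variance is (1 − c) × 0.075. The pooled within-arm variance that the naive analysis uses has expectation 1 − c × (9 + 4)/58. The ratio of true to naive SE is therefore √[(1 − c)/(1 − 13c/58)]:

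- c = 0.05: √(0.950/0.989) = 0.98
- c = 0.10: √(0.900/0.978) = 0.96

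Simulation of a two-sample t-test gives type I error of 4.6% and about 4%. The direction is opposite to Step 1.

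**Step 4: both present.** With cohort and call-group ICC both at 0.05, simulation gives an SE ratio of 1.06 and type I error of 6.4%. Omitting cohort offsets part of the call-group effect but does not cancel it.

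**Step 5: only four groups.** If the group variance is estimated rather than fixed, a Satterthwaite approximation with 3 df for MBI groups and 19 for controls applies. At ICC 0.05: 0.08625² / (0.03625²/3 + 0.05²/19) = 13 df. At 0.02 and 0.10 it gives 15 and 11. The critical values are 2.13, 2.16 and 2.21 against 2.00 on 58 df, so intervals are about 10%, 16% and 26% wider than naive (for example 1.072 × 2.16/2.00 = 1.16).

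**The case against.** **The article does not list the model's terms.** It names a class of model, and that class can carry a group level. An article condenses the full plan, and an analysis plan that is not shown may include group and cohort. This stands as a limit on certainty: a reader might infer that the analysis has been fixed without these terms, and the text does not say so. What remains is that the hierarchy it does describe is longitudinal only, and followed as written it does not match the design.

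**The direction is conditional.** A reader might infer that the standard errors are certainly too small. That requires a positive ICC, which the article does not give. A single instructor removes differences between instructors as a source of correlation. Calendar time is not a source specific to the MBI arm either, because controls in the same cohort share it. Shared peers and session dynamics remain.

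**Cohort works the other way.** A reader might also infer that both omissions make the standard error too small. Step 3 shows that this is wrong for cohort.

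**The calculation is simple.** It covers one time point with full groups, whereas the plan fits trajectories over four assessments including a baseline taken before the MBI starts. Ten is a maximum, and the article itself cites missed clinic appointment rates as high as 46% in this population. The figures are indicative, and smaller groups reduce them.

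**It is a pilot.** Testing is expressly secondary and low power is acknowledged. That lowers the stakes but does not remove them, since tests at 0.05 remain possible and the effect sizes need an honest measure of precision.

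**Conclusion.** The point holds in a limited form. The design is partially nested and blocked by cohort, and the efficacy model as described states no allowance for either feature.

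For the call group, the consequence is a modest overstatement of precision if the ICC is positive. The true SE is 3% to 14% larger than the naive one for assumed ICCs of 0.02 to 0.10 with ten per group, and about 2% to 10% larger with seven. For cohort, the consequence is a slight loss of precision, with no anti-conservative error.

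The documents do not support a claim that the effect sizes themselves are biased; the point estimates are largely unaffected. The harm is confined to the precision carried into a later trial and to any p-values reported. The sizes rest on assumed ICCs and a single-time-point approximation.

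**What to change.** 1. Add cohort (four levels) as a fixed effect in the random coefficients models. It is the randomization block and costs three degrees of freedom.
2. Report the week-6 MBI-control effect size with a sensitivity interval that allows for group clustering in the MBI arm only, treating controls as singletons. Fix the ICC in turn at 0.02, 0.05 and 0.10 and use the analysed group sizes. Apply the clustering to post-baseline scores or to change: baseline is taken before the MBI begins, so a random group intercept across all four assessments would not capture clustering in change.
3. Optionally, report as supportive a partially nested model with a random group effect on the post-baseline or slope component, using small-sample degrees of freedom such as Kenward-Roger. State that four groups estimate the ICC poorly and that a zero estimate does not show the absence of clustering. This should not be the primary analysis: each MBI group is one cohort's MBI arm, about 3 df inform the group variance, and if the degrees of freedom fell towards 3 the critical value would approach 3.18.

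Items 1 and 2 need a few lines of SAS and no new data, so closed recruitment is no obstacle. The downside is somewhat wider intervals: about 3%, 7% and 14% with the ICC fixed and full groups, and more in the supportive model (Step 5).

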## Discussion

This pilot will provide preliminary evidence regarding the feasibility, acceptability, and efficacy of a telephonic MBI for persons with SCD and chronic pain. Considering how difficult it is to manage SCD, pain in particular, this trial will provide valuable insight into whether a telephonic MBI may help improve the care of persons with chronic pain and SCD. We believe the results of this trial will provide significant new insights for the development of future MBIs for persons with SCD and provide additional information regarding the efficacy of a remote intervention for managing a chronic disease.

### Trial status

Participants are no longer being recruited.

## Abbreviations

BPI: Brief Pain Inventory
CBT: Cognitive behavioral therapy
CD: Compact disc
DEMO: Demographic Questionnaire
MAAS: Mindfulness Awareness Attention Scale
MBI: Mindfulness-based intervention
MBSR: Mindfulness-based stress reduction
PCS: Pain Catastrophizing Scale
PHQ-9: Patient Health Questionnaire–9 items
PI: Principal investigator
PROMIS: Patient-Reported Outcome Measurement System
RCT: Randomized controlled clinical trial
SCD: Sickle cell disease
SPIRIT: Standard Protocol Items: Recommendations for Interventional Trials
VOC: Vaso-occlusive crisis
